## Abstract

Suicidal behavior and Non-Suicidal Self-Injuries (NSSIs) are a major health problem in the adolescent population. New technologies can contribute to the development of innovative interventions in suicide prevention. Here, we present the SmartCrisis-Teen study protocol. The study consists of a randomized clinical trial which aims to evaluate the effectiveness of a digital safety plan to prevent suicidal behavior and NSSIs in adolescents. This is a multicentric study which will be conducted among the adolescent population, both in clinical and student settings, with a target sample of 1080 participants. The intervention group will receive an Ecological Momentary Intervention (EMI) consisting of a digital safety plan on their mobile phone. All participants will receive their Treatment As Usual (TAU). Participants will be followed for six months, with weekly and monthly telephone visits and face-to-face visits at three and six months. Participants will be assessed using traditional questionnaires as well as Ecological Momentary Assessment (EMA) and Implicit Association Tests (IATs). With this intervention, we expect a reduction in NSSIs through the acquisition of coping strategies and a decrease in suicidal behavior over the course of follow-up. This study provides a novel, scalable digital intervention for preventing suicidal behavior and NSSIs in adolescents, which could contribute to improving adolescent mental health outcomes globally.

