### 2.3. Sample Size Calculation

Sample size calculation will be performed using G*Power software, version 3.1. Based on previous clinical trials that explore the ability of interventions in SI reduction, in the midterm [36] we estimate an effect size of 0.5. Since the alpha error is set at 5% and the power at 95%, performing the modality “Means: Difference from constant (one sample case)”, the program determined that we would need a minimum of 45 participants per branch. Considering our recruitment capacity and assuming dropouts, we set the sample size at 60 participants per branch (120 in total). In order to stratify by center—so that we can explore the possibility of bias by different recruitment centers—we will try to have this sample size in each of the participating hospitals as well as in the educational contexts, which would result in a total sample of 120 × 9 = 1080 participants.

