### 2.13. Statistical Analysis

Traditional statistical analyses will be performed using SPSS 25.0 statistical software. For continuous variables, we will use t-tests to compare means between groups and ANOVA for multiple group comparisons. For categorical outcomes, chi-square tests will be employed to examine the frequency distributions.

In order to compare suicidal behavior (CSSRS score) at baseline and at the end of follow-up, a Wilcoxon test will be used. Survival curves (time to a new event, defined as a completed suicide, a suicide attempt or a visit to the emergency room for suicidal ideation) will be calculated using the Kaplan–Meier actuarial method.

To assess the feasibility of the project, the participation rate and retention (by percentage and by survival curve using drop-out as an event) will be calculated. To assess the acceptability of the project, descriptive statistics will be provided for the quantitative satisfaction survey and a content analysis will be conducted for the qualitative satisfaction survey. Binary logistic regression will be used to explore the correlation between the study variables, obtaining crude ORs adjusted for age and sex. 

Additionally, to reduce the probability of bias, we will factor by certain variables that could potentially act as confounders, such as the presence of other health apps in the users’ phones and response latency (which will be measured). 

All tests will be two-tailed, with a significance level of *p* < 0.05 and 95% confidence intervals.

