## 4. Expected Results

This project is highly feasible, as the mobile application it uses has already been tested in previous studies in the adult population [35]. With this intervention, we hope to contribute to the mental health of the adolescent population in the following two ways: Firstly, by decreasing suicidal behavior over the course of follow-up, i.e., both suicidal ideation and suicide attempts, which will be reflected in lower CSSRS scores in the intervention group. Secondly, by reducing NSSIs through the acquisition of coping strategies that can be used in times of risk. This training should be a useful tool beyond the follow-up period of the study and could be applied in the long term. As NSSIs increase the risk of a subsequent suicide attempt, it is hoped that reducing NSSI episodes will also reduce suicide risk.

We also expect that The D/S IAT and SI IAT will demonstrate predictive validity with respect to the gold standard CSSRS.

Finally, we also expect the project to be well accepted by the participants, which will be reflected in the satisfaction surveys provided. Demonstrating its feasibility will allow it to be implemented on a large scale.

Monitoring will be a source of information for understanding suicidal behavior, NSSIs and their associated factors. Real-time monitoring will facilitate an individualized approach that will allow for the design of prevention strategies tailored to the uniqueness of each patient. 

Finally, it is important to stress the importance of transmitting to the adolescent population the need to seek help if they find themselves in a situation of suicidal risk. Given that this is a population that integrates mobile devices into their daily lives, it is expected that the demand for help will be more accessible; it is also hoped that the reception of the preventive approach will be improved.

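### Section 2.3 sizes the trial to stratify by centre, but section 2.13 names no centre or cohort term and no effect by cohort, although about 78% of the planned sample appears to be clinical

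*Protocol article*

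**What the plan says.** - **Population.** The abstract describes a trial "conducted among the adolescent population, both in clinical and student settings". Section 2.2 defines three cohorts: patients aged 13–17 with a suicide attempt or NSSI in the previous month, from seven hospitals; screen-positive pupils aged 13–17 from ten Madrid schools; and screen-positive students aged 18–24 at one university.
- **Size.** Section 2.3 takes 60 per arm, 120 in all, and seeks that number in every hospital and in the educational contexts, "which would result in a total sample of 120 × 9 = 1080 participants". The reason given is stratification by centre, to explore bias between recruitment centres. The target is worded as something the investigators will try to reach.
- **Analysis.** Section 2.13 says "For continuous variables, we will use t-tests to compare means between groups and ANOVA for multiple group comparisons". It adds chi-square tests, a Wilcoxon test of CSSRS at baseline against end of follow-up, Kaplan–Meier curves, and logistic regression adjusted for age and sex. The examples of further factors are other health apps and response latency. Neither centre nor cohort is named.
- **Expected result.** Section 4 expects a fall in suicidal ideation and attempts, "which will be reflected in lower CSSRS scores in the intervention group". Sections 4 and 5 speak of adolescents in general and do not separate the settings.

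**The concern.** Stratification by centre is the only reason section 2.3 gives for going from 120 to 1080 participants, yet an analyst who follows section 2.13 as written would not separate the centres or the cohorts.

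The cohorts differ in ways that could change the effect of a safety plan. Entry is by a recent event in one and by a positive screen in the others. Ages are 13–17 in two and 18–24 in the third. The comparator can differ too: sections 2.1 and 2.12 give usual treatment only to those already receiving it, so a student control may have only the EMA and the study contacts.

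If most of the sample is clinical, an unstratified between-arm result is largely a statement about recent attempters and self-harmers. The trial also sets out to answer for school and university settings, and a reader could not tell from that result whether the plan works there.

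**Working it through.** **1. The plan's own figures.** Section 2.3 states: "we estimate an effect size of 0.5", alpha 5%, power 95%, the G*Power option "Means: Difference from constant (one sample case)", and the result "we would need a minimum of 45 participants per branch". An exact noncentral-t calculation for one sample at d = 0.5 gives n = 45 one-sided and n = 54 two-sided. The stated 45 is therefore reproduced as a one-sample, one-sided test. The total also reproduces: 120 × 9 = 1080.

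**2. Share of each cohort.** Section 2.2 has seven hospitals, ten schools and one university. Nine units result only if the schools count as one: 7 + 1 + 1 = 9. With each school counted separately there would be 18 units and 18 × 120 = 2160 participants, which contradicts the stated total. Hence:
- clinical: 7 × 120 = 840, and 840/1080 = 77.8%;
- school: 120/1080 = 11.1%;
- university: 120/1080 = 11.1%.

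**3. What an unstratified comparison would show.** Assume equal SD (set to 1), full recruitment, 1:1 allocation, a two-sided 5% test, an effect d in patients and 0 in students.
- Pooled effect = d × 840/1080. For d = 0.5 this is 0.389.
- SE = √(4/1080) = 0.061, and 0.389/0.061 ≈ 6.4, so power is above 99.9%.

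The 0.5 was entered as a one-sample effect, so treating it as a between-arm difference is an assumption. The range is:

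| Effect in patients (0 in students) | Pooled effect | Power, 540 per arm |
|---|---|---|
| 0.5 | 0.389 | >99.9% |
| 0.3 | 0.233 | 97% |
| 0.25 | 0.194 | 89% |
| 0.2 | 0.156 | 72% |

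**4. What an interaction test could detect.** For clinical against both student cohorts, SE = √(4/N₁ + 4/N₂) and power = Φ(δ/SE − 1.96).
- Full sample (840 v 240): SE = √(4/840 + 4/240) = 0.146. For δ = 0.5, 0.5/0.146 = 3.42 and power is 93%. For δ = 0.3, power is 54%.
- With 25% dropout (630 v 180): SE = √(4/630 + 4/180) = 0.169. Power is 84% for 0.5 and 43% for 0.3. The article gives no dropout rate; 25% is inferred from the rise from 45 to 60 per arm (1 − 45/60).
- For comparison, with the full sample a three-cohort test on 2 degrees of freedom has 87% power for 0.5 and 43% for 0.3. A single contrast of clinical against student settings is therefore the better choice.

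**5. Precision in students.** The 95% half-width is 1.96 × √(4/N).
- Both student cohorts, 180 completers: 1.96 × √(4/180) = 0.29 SD.
- One cohort at 60 per arm: 1.96 × √(4/120) = 0.36 SD. A two-sided test there has 78% power for d = 0.5.

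**The case against.** The strongest reply is that this is detail for an analysis plan. The article is condensed, that plan is not shown, and cohort estimates and interactions usually sit there. As an argument about absence this is fair. What remains is a mismatch inside the article: section 2.3 justifies the sample size by stratification, and section 2.13, which goes as far as naming app use and response latency as factors, does not mention centre or cohort.

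A reader might infer that the cohorts will be pooled and that a positive pooled result will be claimed for students. The documents do not support that. Section 2.13 never says the analysis is pooled, and sections 4 and 5 do not mention students, schools or universities. The text leaves that outcome open but does not announce it.

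Nor can one say that the planned ANOVA ignores treatment effects by cohort. The groups are not defined, the list of factors is open-ended, and section 3 foresees covariance analysis. Centre stratification in section 2.3 would also separate the two student units if it were carried out. Its stated purpose, however, is bias between recruitment centres, so it would not by itself yield an effect in students.

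Two further points stand. The only test that section 2.13 names for the CSSRS score is a before-and-after Wilcoxon test, to which no arm-by-cohort term can be added, so the fix presupposes a between-arm comparison. Section 4 expects lower scores in the intervention group, and section 2.13 provides for between-group tests, so that presupposition is reasonable. And a pooled effect over the enrolled mix is a legitimate summary; the point is that it should not be the only one.

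**Conclusion.** The point holds as a gap between sections 2.3 and 2.13. The sample is sized for stratification, and the stated analysis contains no term or estimate that uses it. On the reading that yields nine units, 77.8% of the planned sample is clinical, so an unstratified result would say little about students. With 0.5 SD in patients and none in students, it would be positive with more than 99% power.

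This rests on four assumptions: the ten schools count as one unit; the recruitment target is met in every unit; SDs are equal; and 0.5 can stand as a between-arm difference. The zero effect in students is a hypothetical used to show what could be masked, not a forecast. Smaller effects in patients lower the pooled power, to 72% at 0.2 SD, but leave the weighting unchanged.

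**What to change.** In section 2.13:
- Fit the between-arm CSSRS comparison with arm and cohort terms, and keep the overall arm effect as a summary.
- Report the arm effect with its 95% CI separately for the clinical, school and university cohorts.
- Add one arm-by-setting interaction test (clinical against student), labelled exploratory. State that its power is about 84–93% for a 0.5 SD difference and only about 43–54% for 0.3 SD, so a non-significant result does not show equal effects.
- Say how the centre stratification of section 2.3 enters the analysis, and state the planned number per cohort so that the 840/120/120 split need not be inferred.
- Base any conclusion about students on the student estimate.

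The cost is wording and one further model on data already collected. The downside is imprecision: about ±0.29 SD for both student cohorts together with 180 completers, and about ±0.36 SD for one cohort at 60 per arm. The student conclusion may therefore be weaker than hoped.

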Here, we present the SmartCrisis-Teen study protocol, a Randomized Clinical Trial whose main objective is to evaluate the effectiveness of a digital safety plan combined with EMA to prevent suicidal behavior and NSSIs in the adolescent population. Our secondary objectives are to determine the feasibility and acceptability of the safety plan and to validate the use of the D/S IAT and SI IAT with respect to the gold standard Columbia Suicide Severity Rating Scale (CSSRS) [34]. Our hypothesis, based on previous studies carried out in the adult population [35], is that there will be a significant reduction in suicidal behavior and NSSIs episodes after the follow-up, which will be translated in lower scores in the CSSRS. As a secondary hypothesis, we expect that the digital safety plan will be feasible and well-accepted and that the D/S IAT and SI IAT will demonstrate adequate external and internal validity.

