#### 2.2.1. Cohort 1: Clinical Setting 

The clinical sample will consist of adolescents with a history of recent suicidal behavior or NSSIs—in the month before recruitment—seen in the emergency department, in the mental health hospitalization unit, or in the mental health outpatient clinics of seven hospitals located in the three Spanish regions of Madrid, Andalusia, and Asturias. 

The inclusion criteria for this group are: Being between 13 and 17 years old.Presenting a suicide attempt or an NSSI in the month previous to recruitment.Being able to understand the project and being interested in participating.Having parents or legal guardians capable of signing the informed consent.Being fluent in Spanish.Owning a smartphone with internet access and iOS or Android operating system.

The exclusion criteria for this group are:Refusal to install the mobile application.Any circumstance or indication that discourages the regular use of a mobile phone (e.g., addiction to new technologies).

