### 2.7. Randomization and Follow-Up

A 1:1 randomization will take place after enrollment, where each participant will be assigned to one of the two groups. In both the control and intervention groups, an initial visit will take place during which a psychiatrist or psychologist will install the MEmind app on the participants’ mobile phone so that they can answer the questionnaires contained in the app with the guidance of the evaluator. In the case of self-administered questionnaires, the participants will answer directly on the screen of their mobile phone. In the case of hetero-administered questionnaires, the evaluator will complete them via the MEmind web portal, which is synchronized with the application.

Participants will be followed for six months, with weekly and monthly telephone visits and face-to-face visits at three and six months. In the intervention group, participants will also be given access to the safety plan included in the MEmind application. During the baseline visit, the plan will be set up for the first time and how it works will be explained. 

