### 2.12. Assessment Criteria

After six months, a before-and-after comparison will be made in both the control and intervention groups. 

Our main outcome will be a reduction in suicidal behavior, as measured by a score on the CSSRS.

Our secondary outcomes will be as follows: The occurrence of suicidal behavior as a clinical event (completed suicide, attempted suicide, ED visit for suicidal ideation, ED visit for self-harm),Predictive validity of the D/S IAT and SI IAT tests to clinical events recorded during follow-up.Acceptability of the project through user-perceived satisfaction.Project feasibility measured by participation and retention.

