## 3. Limitations

This study incorporates several methodologies to address potential biases, though inherent limitations remain. The digital nature of our intervention may introduce skewness when compared to traditional clinical interviews. We plan to mitigate this by employing statistical controls such as covariance analysis to adjust for baseline differences. 

Furthermore, while randomization reduces selection bias, the possibility of non-random dropout exists, which could lead to attrition bias. We will employ intention-to-treat analysis to minimize the effects of dropout. Despite these efforts, some external factors influencing participant engagement with the digital tool may not be fully controllable. We acknowledge these limitations and will discuss their potential impact on our findings, aiming to provide a transparent and critical assessment of our study’s results.

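### No between-arm test is assigned to the primary CSSRS outcome: the only test that names it compares baseline with six months

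*Protocol article*

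**What the plan says.** The trial is randomised with two arms (section 2.7): "A 1:1 randomization will take place after enrollment, where each participant will be assigned to one of the two groups". The primary outcome is in section 2.12: "Our main outcome will be a reduction in suicidal behavior, as measured by a score on the CSSRS". The sentence before it sets the comparison: "After six months, a before-and-after comparison will be made in both the control and intervention groups". Section 2.13 then gives the CSSRS its test: "In order to compare suicidal behavior (CSSRS score) at baseline and at the end of follow-up, a Wilcoxon test will be used".

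Two other places follow the same before-after logic:

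- **Section 1.** The hypothesis is that "there will be a significant reduction in suicidal behavior and NSSIs episodes after the follow-up", with no reference to the control arm.
- **Section 2.3.** The sample size uses the G*Power option for a mean against a constant (one-sample case), with effect size 0.5, alpha 5% and power 95%. This gives 45 per branch, raised to 60, then 120 × 9 = 1080 in total.

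Three places point towards a comparison of arms:

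- **Section 2.13** opens with a general rule of t-tests between groups for continuous variables.
- **Section 3** mentions "employing statistical controls such as covariance analysis to adjust for baseline differences" and intention-to-treat analysis.
- **Section 4** expects "lower CSSRS scores in the intervention group".

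None of these three assigns a between-arm test or model to the CSSRS.

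**The concern.** A pre-post test asks whether scores changed. It does not ask whether they changed more with the safety plan than without it. In this trial change is likely whatever the plan does. Cohort 1 qualifies by "Presenting a suicide attempt or an NSSI in the month previous to recruitment", and cohorts 2 and 3 by a positive screen. People selected at a high point tend to score lower later. Both arms also receive EMA, follow-up calls and visits and, where already in care, usual treatment. Everything the arms share enters the pre-post change, and only the contrast between arms removes it.

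If the stated test is taken as the primary analysis, a significant fall in the intervention arm could be reported as efficacy when the plan did nothing. At the planned total size that outcome would be close to certain under quite modest natural improvement.

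**Working it through.** **1. Reproducing the plan's own figure.** Inputs from section 2.3: d = 0.5, alpha 0.05, power 0.95, one-sample t-test. Power = 1 − F(t_crit; n − 1, d√n), where F is the noncentral t distribution function (the two-sided version adds the lower tail).

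| Version | n | Power |
|---|---|---|
| One-sided | 44 | 0.947 |
| One-sided | 45 | 0.951 |
| Two-sided | 45 | 0.907 |
| Two-sided | 54 | 0.950 |

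The stated 45 is reproduced exactly, but only as a one-sample, one-sided test. The trial was therefore sized for a change within one group, in line with the pre-post test. The one-sided basis also disagrees with section 2.13, which makes all tests two-tailed.

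**2. What a pre-post test does with an inert plan.** Assumption: no treatment effect, and the same standardised change δ in both arms. The documents give no value, so δ runs from 0.2 to 0.5. The probability that the intervention-arm test is significant (two-sided 5%) is the one-sample power at noncentrality δ√n. For n = 60 and δ = 0.3, the noncentrality is 0.3 × √60 = 2.32 and the power is 0.63. The simulated columns use 2000 trials per row, with normal changes, a Wilcoxon signed-rank test and 60 per arm.

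| δ | n = 60, t formula | n = 60, simulated Wilcoxon | n = 540, t formula | Between-arm t-test, n = 60, simulated |
|---|---|---|---|---|
| 0.2 | 33% | 31% | 99.6% | 5.5% |
| 0.3 | 63% | 64% | >99.9% | 6.2% |
| 0.4 | 86% | 85% | >99.9% | 4.1% |
| 0.5 | 97% | 96% | >99.9% | 4.8% |

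The last column should be 5%, because the plan is inert; the spread is simulation error.

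**3. Sizing a between-arm test.** Two-sample t-test, two-sided 5%, noncentrality d√(n/2) with n per arm.

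- d = 0.5, power 95%: n = 104 gives 0.948 and n = 105 gives 0.950, so 105 per arm.
- d = 0.5, 60 per arm: noncentrality 0.5 × √30 = 2.74, power 78%.
- d = 0.5, 45 per arm: power 65%.
- d = 0.5, 540 per arm (1080 / 2): power above 99.9%.
- d = 0.2, 540 per arm: noncentrality 0.2 × √270 = 3.29, power 91%. With 480 per arm analysed it is 87%.

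These figures treat 0.5 as a between-arm standardised difference. Section 2.3 gives the number without saying which scale it is on, and a standardised within-person change is a different quantity. Adjustment for baseline is not counted.

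**The case against.** The best defence is that the document does not rule out a comparison of arms. The Wilcoxon sentence does not itself say that the test is run within each arm; that comes from section 2.12. The general t-test rule could be read to include the CSSRS score, the covariance analysis in section 3 could be the adjusted comparison, and section 4 can be read as expecting a difference between arms. This is also a condensed article, and a separate analysis plan may match tests to outcomes.

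Part of this stands. A reader might infer that the randomised comparison will not be tested at all, or that the randomisation is thrown away. The documents do not support that: between-group tests are mentioned and could reach the CSSRS. What they show is narrower. No such test is assigned to it, and the one test that names it is pre-post. The appeal to an unseen plan does not remove this, because the article states a before-after comparison for the main outcome rather than staying silent.

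A reader might also infer that efficacy will be claimed when the intervention arm is significant and the control arm is not. No passage states that rule. If it were used with an inert plan and 60 per arm, it would mislead in p(1 − p) of trials: 22%, 23%, 12% and 3% for changes of 0.2, 0.3, 0.4 and 0.5. The point does not rest on it.

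**Conclusion.** The concern holds in this form: the primary CSSRS outcome has no between-arm test assigned to it, while sections 1, 2.3, 2.12 and 2.13 all follow before-after logic. A significant pre-post fall in the intervention arm would not show that the plan works. With an inert plan and an equal change in both arms it would appear in about 33% to 97% of trials at 60 per arm, and in 99.6% or more at 540 per arm.

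The size of the problem rests on an assumed natural change of 0.2 to 0.5 SD and on approximately normal changes. Its direction rests only on the entry criteria and on the care that both arms share. It should be corrected before analysis; the data needed are already planned.

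**What to change.** 1. **Sections 2.12 and 2.13.** Make the primary analysis the between-arm comparison of the six-month CSSRS score, by arm as randomised, adjusted for baseline CSSRS and recruiting centre or context. Use ANCOVA, or a proportional-odds model if the score is ordinal or skewed. Report the adjusted difference (or odds ratio) with its 95% CI. Keep the within-arm Wilcoxon tests as descriptive only.
2. **Section 1.** Reword the hypothesis as intervention versus control.
3. **Section 2.3.** Restate the sample size as a two-sample, two-sided calculation, say which scale the effect size of 0.5 is on, and separate the power of the pooled trial from that of one centre.

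The cost is wording in sections 1, 2.3, 2.12 and 2.13. No new data and no extra enrolment are needed, because the pooled 540 per arm gives about 91% power even at d = 0.2. The price is that a single centre with 60 per arm can no longer be described as powered at 95%: at d = 0.5 it has about 78%, against 105 per arm needed.
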